## Process evaluation

Intervention reach and retention will be assessed by tracking the number of students engaged in the program throughout delivery (n= and proportions reported). Tracking of program participant engagement will occur through fidelity sheets filled out at the end of each student workshop. Fidelity will be measured by facilitators recording deviations from planned content delivery through fidelity sheets. Acceptability and sustainability will be assessed through interviews at the end of the intervention with external stakeholders and program facilitators, paying particular attention to whole-of-school buy-in, resourcing, stakeholder engagement and adaptability.

## Qualitative analysis

All interviews and focus group data collected during the process and outcome evaluation will be recorded using a digital device or using the record feature on Teams/Zoom and transcribed by a professional transcription service. Informed by the theory-driven approach of realist evaluation, this study aims to answer *what works, for whom, under what circumstances and how*. We aim to do this by examining how intervention outcomes are determined by mechanisms that are set off in specific contexts, otherwise known as “context-mechanism-outcome configurations” (Pawson & Tilley, 1997; Pawson et al., 2005). Data on context and mechanisms will be collected using interviews with students and external stakeholders and focus groups with program facilitators and school staff. The data will then be analysed thematically, facilitated by NVivo 14, and the realist program theories will be tested and refined. This process of refinement will be iterative, occurring throughout the study as emerging data are collected and analysed.

| CMO 1: Respect                                                       |                                                                                                                                                                                                                      |                                                                                                   |
|-----------------------------------------------------------------------------|----------------------------------------------------------------------------------------------------------------------------------------------------------------------------------------------------------------------|---------------------------------------------------------------------------------------------------|
| Context                                                              | Mechanism                                                                                                                                                                                                     | Outcome                                                                                    |
| Culture of respect within classroom where students give and receive respect | 
Resource: Classroom teacher demonstrates high regard for their students
 
Reasoning: Students feel respected and emotionally safe. Students decide to engage positively with the Laurel House curriculum
 | Students increase their knowledge and skills, leading to a reduction in harmful sexual behaviours |

#### **CMO 2: Expert facilitation**

| Context                         | Mechanism                                                                                                                                                                                                                            | Outcome                                                        |
|----------------------------------------|---------------------------------------------------------------------------------------------------------------------------------------------------------------------------------------------------------------------------------------------|-----------------------------------------------------------------------|
| Lessons are led by expert facilitators | 
Resource: The expertise and experience of Laurel House facilitators enables them to confidently and sensitively deliver the lessons
 
Reasoning: Students notice the facilitator is highly skilled. They feel trusting and safe
 | Students build more knowledge about consent and healthy relationships |

## Monitoring

### Data monitoring and interim analysis

A Data Monitoring Committee (DMC) will be established comprising of four independent (from the sponsor) researchers including a chair (TBC). Participants will be external to LTU with at least one international member. The DMC will:

- protect and serve trial participants, to assist and advise the lead, chief (CIs) and associate investigators and therefore protect the legitimacy and integrity of the trial;
- safeguard the interests of trial participants, assess the safety and efficacy of the intervention during the trial and monitor the overall conduct of the study.

Each month of the trial, a member of staff at each enrolled school will report any adverse event arising from the intervention using a REDCap online form. Any adverse events that might plausibly be caused by the intervention will be immediately reported to the governing Human Research Ethics Committee, the Trial Management Committee (TMC) and the Data Monitoring Committee. An adverse event may include but is not limited to 1) a non-life

threatening physical injury that requires medical or psychological care, and 2) death, whether by suicide or murder.

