### Data set

**Primary registry and trial identifying number:** ANZCTR number pending

**Date of registration in primary registry:** TBC

**Secondary identifying numbers:** NA

**Source(s) of monetary or material support:** Department of Social Services, Australian Government.

**Primary sponsor:** La Trobe University

**Contact for public queries:** [name]- Senior Manager, Research Ethics, Integrity & Biosafety. Address: [name]  
[contact] Email: [[contact]](mailto:[contact])

**Public title:** Evaluating a Sexual Violence Primary Prevention program (SEP) in Australian Secondary Schools: A Protocol for a Cluster Randomised Controlled Trial

**Scientific title:** A parallel, two-arm cluster randomised controlled study of Year 9 students at 12 Australian secondary schools to evaluate the effectiveness of a sexual violence primary prevention program on students' knowledge, attitudes and behavioural intentions.

**Countries of recruitment:** Australia

**Health condition(s) or problem(s) studied:** Sexual violence, mental health

**Intervention:** Active comparator - Secondary school students receiving sexual violence primary prevention program. Control comparator – Waitlist of Secondary School students (receiving usual school curriculum) with no receipt of a sexual violence primary prevention program.

**Key inclusion and exclusion criteria:** Ages eligible for study: Year 9 secondary school students (approximately 13-15 years old). Sexes eligible for study: both.

**Inclusion Criteria:** Secondary school students in Year 9, secondary school students attending public schools in northern Tasmania.

**Exclusion criteria:** Secondary school students outside Year 9, private school students, students whose parents opt-out of their young person's participation in the trial.

**Study type:** Interventional. Allocation: 1:1. Intervention model: parallel assignment.

**Masking:** Blinded outcomes assessor. Primary purpose: prevention.

**Date of first enrolment:** June 2025

**Target sample size:** Clusters n=12; Students n=180

**Recruitment status:** Recruitment not yet commenced

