### **Choice of comparators**

To better understand the role of consent and healthy relationships education in the prevention of sexual violence, we will measure outcomes across 12 schools in Tasmania, Australia. Of the 12 schools, six schools will be randomly assigned to the intervention group and six schools to the waitlist control group. The control group will not receive the prevention program during the trial, but for ethical reasons will receive the intervention in 2026 after the study has concluded.

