## Assignment of intervention

### Allocation-Sequence generation, concealment mechanism, implementation and blinding

Schools (clusters) will be randomised using a remote system set up by the LTU Statistics Platform. The allocation sequence will be stored on a secure server and concealed from all personnel involved in the trial. It will be created, using computer-generated random numbers, by a statistician with no link to, or contact with, any of the participating schools.

Randomisation will be stratified by the following five variables:

1. Year 9 student population (size)
2. Region of Tasmania
3. Index of Relative Socio-Economic Disadvantage, by suburb and locality (IRSD)
4. Indigenous enrolment, percentage
5. Index of Community, Socio-Educational Advantage (ICSEA)

Once all schools have been confirmed and baseline forms completed, LH will contact the Statistics Platform requesting the randomised assignment of all schools. These assignments will then be communicated to the schools by FH. Prior to baseline form completion all trial team members, schools, and students will be blinded; after this point, all will be unblinded.

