## Harms and auditing

See SAE reporting template -Appendix O2. Any adverse events and or unintended effects of the trial will be monitored by the DMC and TMC and decisions made to terminate the trial if necessary.

As this is not a clinical trial, formal auditing processes by the sponsor will not occur. See DMC detail on assessment of project conduct, safety and adverse events.

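### Adverse events are reported only if school staff attribute them to the programme, which leaves the DMC without a control-arm background rate and does not fit the protocol's other safety wording

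*Protocol*

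**What the plan says.** The protocol has one operative rule for collecting adverse events, under Data monitoring and interim analysis. Each month, "a member of staff at each enrolled school will report any adverse event arising from the intervention using a REDCap online form". The next sentence adds a second test, for escalation to the ethics committee, the Trial Management Committee (TMC) and the DMC: "Any adverse events that might plausibly be caused by the intervention will be immediately reported".

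The same section charges the DMC to "assess the safety and efficacy of the intervention during the trial". Harms and auditing is worded more widely: "Any adverse events and or unintended effects of the trial will be monitored by the DMC and TMC", with termination of the trial among the possible decisions. It refers to an SAE template (Appendix O2), which is not reproduced.

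Two other sections bear on the rule. Choice of comparators states: "The control group will not receive the prevention program during the trial". The allocation section states: "Prior to baseline form completion all trial team members, schools, and students will be blinded; after this point, all will be unblinded".

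**The concern.** Relatedness is normally assessed after an event has been recorded. Here it decides whether the event is recorded at all, and the decision falls to a school staff member who knows the allocation. Control schools are enrolled and so are asked for the monthly form, but with no programme running they have nothing to attribute to it.

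The students are 13 to 15 years old. Sessions Two and Three cover image-based abuse, non-fatal strangulation and child sexual abuse material. The events that the protocol names (injury needing medical or psychological care, and death including suicide) also occur without any programme. A single case is hard to attribute, and a concurrent control rate is what helps the DMC to judge whether a count is unusual. Under the rule as written that rate is not collected. An excess that staff do not link to the programme would leave no trace, and no analysis plan can recover events that were never recorded.

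**Working it through.** **1. The passages side by side**

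| Protocol section | Scope of events | Consequence |
|---|---|---|
| Data monitoring, collection sentence | Events attributed to the intervention | Control schools have essentially nothing to report |
| Data monitoring, escalation sentence | Events plausibly caused by the intervention | Largely redundant if everything collected is already attributed |
| Harms and auditing | Any adverse event or unintended effect of the trial | Wider than what is collected; no other collection route is given |
| Data monitoring, DMC remit | Safety of the intervention | No control rate to set it against |

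An upset caused by the survey in a control student shows the mismatch. It is an effect of the trial, so the DMC and TMC are to monitor it. It does not come from the intervention, so the collection sentence does not ask for it.

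**2. Size, as an illustration**

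The protocol states no adverse-event rate, so there is no figure of its own to reproduce. The only input from it is the target in Data set, "Clusters n=12; Students n=180", allocated 1:1, which gives 180 / 2 = 90 students per arm. Background risk and the share of events that staff attribute are assumptions. There is no true difference between arms.

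- Events occurring per arm = 90 × background risk.
- Expected reports, intervention arm = 90 × background risk × attributed share.
- Expected reports, control arm = 0 on the literal wording.

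| Background risk | Events occurring, each arm | Reported, 25% attributed | Reported, 50% | Reported, 100% | Reported, control |
|---|---|---|---|---|---|
| 2% | 1.8 | 0.45 | 0.9 | 1.8 | 0 |
| 5% | 4.5 | 1.125 | 2.25 | 4.5 | 0 |
| 10% | 9 | 2.25 | 4.5 | 9 | 0 |
| 20% | 18 | 4.5 | 9 | 18 | 0 |

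At 5% background and 50% attribution, treating students as independent, the chance of at least one intervention-arm report is 1 − (1 − 0.05 × 0.5)^90 = 1 − 0.975^90 = 0.90.

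The reported count cannot separate risk from attribution:

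- No effect, 5% risk, 50% attributed: 90 × 0.05 × 0.50 = 2.25 against 0.
- Risk doubled to 10% in the intervention arm, 25% attributed: 90 × 0.10 × 0.25 = 2.25 against 0.

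The two situations give the same expected reports. If staff attribute none of the events, a doubling from 4.5 to 9 is recorded as 0 against 0. As a gauge only, 6 against 0 out of 90 gives a Fisher p of 0.029, ignoring clustering, although the zero comes from the rule and not from an observed absence of events.

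**3. Denominator**

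The 90 per arm is the survey target. The programme goes to Year 9 students generally, and Recruitment gives about 900 students in 12 schools: 900 / 12 = 75 per school, or about 450 per arm if the schools split evenly. All expected counts above would then be five times larger (450 / 90). The pattern does not change.

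**The case against.** The strongest reply is that the sentence is loosely drafted and that wider collection was intended. Asking every enrolled school for a form is pointless if control schools cannot report. A second causality test makes sense only if unrelated events are also collected. Harms and auditing speaks of effects of the trial. Appendix O2, and the terms of reference cited as Appendix O1, are not shown and may define events more widely. This may all be so. But the sentence that staff would follow says otherwise, and a wider appendix would conflict with it. The reply therefore supports correcting the text.

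Other points stand and limit the claim:

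- **No stated analysis is broken.** Harms are neither an objective nor an outcome, and no between-arm comparison of harms is planned. A reader might infer that a planned randomised safety comparison is lost; the protocol does not contain one.
- **Control schools are not certain to report zero.** A reader might infer that they cannot report at all. Control students complete surveys with sensitive items, and a school could well report a survey-related event, especially in view of the wording under Harms and auditing. The zero is what the literal collection sentence yields, not a forecast.
- **The DMC need not be misled.** It would know that control schools run no programme and need not read their silence as a true zero. It would still lack the rate.
- **The rates are assumed, and clustering is ignored.**
- **The narrow rule may have a privacy reason.** Consent describes parental agreement to the survey and/or interview, and Data management limits collection to necessary personal data.
- **Wider collection gives no clean comparison.** Staff remain unblinded, and the logic model (Figure 1) expects more disclosures and referrals when the programme works.

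**Conclusion.** The point holds as a defect in the collection rule and an inconsistency between Data monitoring and Harms and auditing. It should be corrected before the first monthly form is issued. As written, unblinded staff judge causation at the point of collection, control schools would report essentially nothing, and the DMC would carry out its safety remit without a background rate.

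The consequence cannot be sized from the document. The illustration shows only that reported counts would reflect attribution as much as risk. It rests on assumed background risks of 2% to 20%, assumed attribution of 25% to 100%, 90 students per arm and independence between students. Even with full collection, about 180 enrolled students in 12 schools would support a descriptive comparison only. The conclusion also assumes that the unseen appendices do not already set a wider rule. If they do, the protocol sentence must still be brought into line.

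**What to change.** Reconcile the collection sentence under Data monitoring and interim analysis with Harms and auditing and Appendix O2, so that:

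1. All 12 schools report the same defined events over the same period, whatever the presumed cause.
2. The population is stated, is one that staff can identify, and does not leave out Year 9 students who attend the programme without joining the survey. Under Consent, agreement runs through REDCap and the researchers, and no step tells a school who has enrolled. Limiting reports to enrolled students could therefore be unworkable and could drop exposed students.
3. Relatedness is a separate field, completed after the event is recorded and where possible by someone unaware of arm.
4. The plausibility test is kept for immediate reporting only.
5. The DMC receives counts by arm, with disclosures and referrals tabulated apart from harms because the programme is expected to raise them.

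**Cost.** The form already goes to every school and no sample-size figure changes. Staff would report more: about 15 students per school if only enrolled students are covered, about 75 if all of Year 9 is. Recording unrelated events in minors, particularly in control schools, may need an amendment to the ethics or consent wording. Ascertainment stays unblinded, so the counts by arm need cautious reading.

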### Session Two

This session delves into legal aspects of consent and emerging forms of sexual violence. With expert insights from a women's legal service lawyer, the session will explore: 1) legal definitions of consent, 2) image-based abuse, 3) non-fatal strangulation (sexual choking), stealthing and the law, 4) and guidance on accessing legal support and counselling.

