| Program materials
Full-time educators,
Part-time practice champion
Regular internal and external supervision
Partnership with Women's Legal Service Tasmania
Evidence-based practice
Laurel House expertise and readiness
School buy-in and readiness
Crisis and counselling support
In-kind funding
Funding from Department of Social Services (DSS) | Resource development
Co-design with schools
Program adaptation
Educational session with school staff
Educational session with parents/carers
Educational sessions with students
School Student Champions
Management of disclosures by students, parents or school staff
Post-program reflection and revision
Managing key stakeholder relationships | Consistent student attendance and engagement at workshops
Teachers are upskilled and confident to take messages forward beyond program
Attendance and engagement of teachers and parents/carers at educational sessions
Increased knowledge and awareness among students about consent and the law; porn literacy; the gendered drivers of sexual violence; and how to access support services. | Adoption of respectful and consensual behaviours in relationships
Positive attitude shifts in relation to myths about sexual violence and gender stereotypes
Increased disclosures by victim-survivors
Improved student skills in relation to bystander techniques and understanding consent
Increased referrals to specialist services | Promote change to the school's socioecology on an individual, relational, and community level to address the drivers of sexual violence
Better informed and responsive parents and carers
Advance the evidence-base for primary prevention interventions in school settings |

**Figure 1:** Schools Education Program logic model

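### The adverse-event description is open-ended, but its two examples fit this programme poorly and reporting depends on staff attributing cause, so a nil report would be weak evidence on psychological harm

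*Protocol*

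**What the plan says.** The protocol describes adverse events once, under Data monitoring and interim analysis. The sentence opens "An adverse event may include but is not limited to 1) a non-life" and continues "threatening physical injury that requires medical or psychological care, and 2) death, whether by suicide or murder".

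The same section sets the route: every month, "a member of staff at each enrolled school will report any adverse event arising from the intervention using a REDCap online form". It also sets an expedited path: "Any adverse events that might plausibly be caused by the intervention will be immediately reported to the governing Human Research Ethics Committee", together with the two trial committees.

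Harms and auditing adds that "Any adverse events and or unintended effects of the trial will be monitored by the DMC and TMC", and that these committees may decide to end the trial. It refers to a form for serious events ("See SAE reporting template -Appendix O2"), which is not part of the document at hand.

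On content, Session Two includes "non-fatal strangulation (sexual choking), stealthing and the law" as well as image-based abuse. Session Three covers pornography and child sexual abuse material. The logic model in Figure 1 lists "Crisis and counselling support" among the inputs, the handling of disclosures among the activities, and more disclosures by victim-survivors among the intended outcomes.

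**The concern.** Examples in a definition tell the person filling in a form what kind of event is wanted. Here one example is bodily injury of limited severity and the other is death from two specific causes. The intervention is three classroom sessions of talk and small-group work. The reactions one would look for first are distress, re-traumatisation and, at the severe end, suicidal behaviour. The examples do not point there.

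The data monitoring committee is charged with assessing safety during the trial, and the monthly school form is the only dedicated route for collecting harms that the protocol describes. If that route picks up the foreseeable harms only when a staff member thinks to report them, the committee's picture of safety is thin exactly where it matters. A published statement that no adverse events occurred could then be read as more reassuring than it is.

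**Working it through.** No figure in the protocol needs reproducing, because the point turns on wording. The check is to take each kind of event and ask whether either example names it and whether the general wording still reaches it.

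| Kind of event | Example 1 (injury) | Example 2 (death) | Reached by the open-ended wording? |
|---|---|---|---|
| Physical injury needing care, not life-threatening | named | – | yes |
| Self-inflicted injury needing care, not life-threatening | fits | – | yes |
| Life-threatening injury or suicide attempt, non-fatal | not named, because the example stops short of life-threatening | not named | yes |
| Suicidal ideation without injury | not named | not named | yes |
| Acute distress without injury | not named, because psychological care is mentioned only as following a physical injury | not named | yes |
| Death by suicide or murder | – | named | yes |
| Death from another cause | – | not named | yes |

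Two gaps follow. One is of severity: nothing is named between a lesser injury and death. The other is of type: no psychological harm is named unless it comes with a physical injury.

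The next step is to see what the open-ended wording depends on in practice.

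1. **Attribution at the point of reporting.** Schools are asked for events they consider to come from the intervention. A staff member must judge cause before anything is recorded, and an event judged unrelated leaves no trace.
2. **Knowledge of allocation.** Under Assignment of intervention, everyone is unblinded once baseline forms are complete. The attribution is therefore made by people who know which arm their school is in.
3. **Control schools.** They receive only the usual curriculum during the trial. Although every enrolled school is to report, a control school has almost nothing that could qualify as coming from the programme. Its count will be near zero by construction, so the arms cannot be compared.
4. **Other sources.** The student survey measures knowledge, attitudes and intentions. Fidelity sheets record attendance, implementation challenges and departures from planned content. Neither is set up to collect harms. The unintended effects mentioned under Harms and auditing have neither a definition nor a collection route of their own.
5. **Seriousness.** A template for serious events is cited, but the text does not say which events are serious.

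**The case against.** The strongest reply is that the list is illustrative. The text says events are not limited to the two examples, asks for any event attributable to the programme, and sends any plausibly related event onward at once, whatever its type. This stands, and it rules out several stronger readings:

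- A reader might infer that life-threatening events and psychological harms fall outside reporting. They do not; they are unnamed.
- A reader might infer that self-harm fits neither example. A self-inflicted injury that needs care and is not life-threatening fits the first.
- A reader might infer that reporters have no other definition to work from. The REDCap form and Appendix O2 are not shown, and either may list further categories.
- A reader might take the counselling input in the logic model as proof that the sponsor expects psychological adverse events. It shows only that support and disclosures were planned for.
- A reader might attach an upper confidence limit to zero events among the 90 students per arm (180/2). That is the survey target, not the number exposed: the Recruitment section puts students in the interested schools at about 900. The calculation would also ignore clustering, and any distress rate set against it would be invented.

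It can also be said that facilitators note difficulties after each session and that unintended effects are to be monitored. Both are true, but neither sets a criterion or a reporting route for psychological harm. The open-ended phrase likewise permits such reports without prompting them, and it does nothing about the attribution filter or the missing control comparison.

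**Conclusion.** The point holds as a weakness of wording and reporting route. It is not an exclusion of harms. The two examples leave life-threatening non-fatal events, deaths from other causes and distress without injury unnamed, in a trial whose content makes distress foreseeable. Capture of those harms rests on unblinded staff who report only what they attribute to the programme.

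A nil report would therefore be weak evidence on psychological harm. To call it meaningless would go too far, since a conscientious reporter may and should report such events under the present text. No numerical size can be given. The conclusion assumes that the unseen form and appendix do not already supply a fuller list. If they do, the gap in the examples is mostly presentational, but the reliance on attribution remains as the protocol is written. The change is a worthwhile low-cost improvement, and the trial does not stand or fall on it.

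**What to change.** Under Data monitoring and interim analysis, and on the REDCap form and Appendix O2 where they do not already do so, replace the two examples with a list that has no severity gap:

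- psychological distress needing support, with or without injury;
- self-harm, suicidal ideation or suicide attempt;
- victimisation or bullying linked to trial content;
- any physical injury needing care, including life-threatening injury;
- death from any cause.

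State which of these count as serious, so that the cited template has a defined trigger. Ask schools in both arms to report every listed event regardless of presumed cause, and record relatedness in a separate field. The existing rule for immediate onward reporting can then draw on that field. Count disclosures of past experience apart from adverse events, since more disclosure is an intended outcome of the programme.

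The cost is one protocol paragraph and a few form fields, best settled before first enrolment in June 2025. The downside is more reports for schools and the data monitoring committee to handle, including background events in control schools. Staff would still know their arm, so a difference in vigilance between arms would remain and should be acknowledged when the counts are compared.
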